#### Moderator analysis plan

Potential moderators of intervention effects for the study primary and secondary outcomes will be examined using interaction tests in the linear mixed models. Subgroup analyses will be conducted for preregistered moderator variables with significance of the group-by-moderator interaction where p≤0.10: *age* (dichotomised at the median), *baseline psychological distress* (DASS-21, normal-to-mild (<41) vs moderate-to-extremely severe (41+)), *baseline nature connection* (Connection with Nature Instrument (CN-12) score, weak (<5) vs moderate-to-strong (5+)), *baseline emotional control* (Conformity to Masculine Norms-46 (CMNI-46) emotional control subscale, greater restraint (<2) vs lower restraint (2+)) and *baseline physical activity level* (International Physical Activity Questionnaire (IPAQ) short form, inactive vs minimally active/high active).

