## Introduction

 In Australia and internationally, the burden of depressive disorders in men is growing.^1–3^ Between 1990 and 2021, both the total number of men with depression and the years of healthy life lost to depression have almost doubled globally.^3^ Current estimates suggest one in eight men will now experience depression over the lifespan.^4^ These data are also reflected in Australia, where depression is one of the most common mental health disorders in men.^5^

Despite recent increases in men’s help-seeking,^6^ men remain less likely to seek psychological support than women.^7–9^ For example, in Australia, 51% of women experiencing psychological distress consulted a health professional, compared with 37% of men.^5^ In a report from the world’s largest longitudinal men’s health study,^10^ only one-quarter of men indicated that they were likely to seek help from a mental health professional if they experienced an emotional or personal problem.^11^ This help-seeking gap may in part explain why women are twice as likely to be diagnosed with depression, yet men are three times more likely to die by suicide.^12–14^

These data suggest that current mental health treatment options are not engaging large numbers of men who need help. For example, while psychotherapy is effective for treating depression,^15^ estimates suggest up to 45% of men drop out of therapy prematurely.^16^ One contributing factor is that conventional indoor therapy settings may not align with men’s preferences or social conditioning. The dominant cultural narrative around masculinity in many western countries, including Australia, rewards emotional stoicism and self-reliance,^17
18^ making it challenging for many men to express vulnerability in the formal, face-to-face structure of conventional therapy. This discomfort is a key reason cited for discontinuing therapy, with many men reporting that therapy ‘didn’t feel right’.^16^ While this may reflect the complexity of engaging and assisting men with mood disorders, it reinforces the need for gender-specific treatments that men with depression find appealing.^19
20^

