Emotional control	Conformity to Masculine Norms-46 (CMNI-46): Emotional Control subscale	^ 62 ^	6	I hate it when people ask me to talk about my feelings	4-point scale: Strongly disagree (1) to strongly agree (4)	X		
Nature connection	Connection with Nature Instrument (CN-12)	^ 63 ^	12	I feel right at home when I am in nature	7-point scale: Strongly disagree (1) to strongly agree (7)	X	X	
Nature contact	Nature Contact	^ 64 ^	1	Over the past month, approximately how many hours per week on average would you consider yourself to have interacted with nature? For example, walking outside, biking, gardening, playing games/sports, camping, fishing, reading outside, yard work, hanging out in a park, etc	Open response	X	X	
Other measures								
Therapy expectancies and preferences	Treatment Acceptability Preferences Scale (TAPS): Expectancies	^ 65 ^	8	How effective do you think this approach would be for improving your mood?	5-point scale: Not at all (0) to very much (4)	X		
	Treatment Acceptability Preferences Scale (TAPS): Preference		1	Do you have a preference for one of the two approaches to therapy?	No; yes - outdoor walk-and-talk; yes - conventional indoor	X		
Therapeutic process indicators	Individual Therapy Process Questionnaire (ITPQ): Global Alliance and Patient Fear subscales	^ 66 ^	5	Today, I felt comfortable in the relationship with the therapist (Global Alliance) Today, it was difficult for me to talk openly with the therapist (Patient Fear)	5-point scale: Does not apply (0) to fully applies (4)	*		

* Measure completed via texted survey after participants’ first, middle and final session.

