Strengths of this study protocol include a randomised design with an active intervention control group (conventional indoor therapy), a preregistered, detailed statistical analysis plan that will follow the intention-to-treat principle and the inclusion of a 12-month follow-up to measure the longer-term treatment outcomes. In addition to measuring overall psychological distress (depression, anxiety and stress), a comprehensive range of secondary outcomes will also be assessed to capture other psychological (male-type depression symptoms, mental well-being, suicidal ideation, quality of life), behavioural (physical activity, sleep, nature contact), social (nature connection, emotional control, engagement in valued activities, mental restoration) and economic (costs) impacts of the programme. By successfully completing this trial, insights into the efficacy of an innovative psychotherapy approach for men will be generated through various analytical methods (eg, mediation and moderation analyses). Lastly, recruitment efforts will focus on men residing in areas identified as socio-economically disadvantaged to ensure a diverse sample. Limitations of the current study include reliance on psychologist self-report to assess adherence to the therapy modality, as sessions are not independently coded. This approach was necessary due to the practical challenges of recording sessions in outdoor settings; however, it may introduce bias into the fidelity assessment. Furthermore, data relating to therapist favourability to a particular therapy setting were not collected, which may represent an additional source of bias; future trials building on this work would benefit from collecting therapist allegiance data to enable assessment of its potential influence in sensitivity analyses. The power calculation did not account for therapist-level clustering; the extent to which this affects statistical power will depend on the magnitude of the therapist-level intraclass correlation coefficient, which will be reported alongside the trial outcomes. In addition, participants self-select into a trial conducted at a university campus, which may limit generalisability to other clinical populations and health service settings. Individuals who are willing to participate in such trials may be more motivated or more receptive to novel therapeutic approaches than the general population. As such, further research will be needed to evaluate this intervention when implemented within routine care contexts.

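### The emotional-control subgroup labels run against the scale direction printed in Table 1, so an effect on this one moderator could be attributed to the wrong men

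*Protocol article*

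**What the plan says.** The Moderator analysis plan names five preregistered moderators and conditions subgroup analyses on "significance of the group-by-moderator interaction where p≤0.10". For baseline emotional control the two groups are "emotional control subscale, greater restraint (<2) vs lower restraint (2" and above).

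Table 1 (Survey measures) identifies the instrument as "Conformity to Masculine Norms-46 (CMNI-46): Emotional Control subscale", with six items. The response format is "4-point scale: Strongly disagree (1) to strongly agree (4"), the example item is "I hate it when people ask me to talk about my feelings", and only the baseline column is marked. The row sits under the secondary outcomes.

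The Discussion lists the measure again among the outcomes meant to capture programme impacts: "social (nature connection, emotional control, engagement in valued activities, mental restoration").

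Neither Table 1 nor the Moderator analysis plan mentions reverse scoring of this subscale.

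**The concern.** Agreeing with the example item expresses emotional restraint, and agreement earns the higher number. A higher score should therefore mean more restraint, yet the plan gives the greater-restraint label to the low scorers.

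This moderator bears on the trial's rationale. The Introduction explains men's difficulty with conventional therapy partly by a cultural narrative that "rewards emotional stoicism and self-reliance", and the section on walk-and-talk therapy argues that walking side by side eases the discussion of sensitive topics. Whether more restrained men gain more from the outdoor format is a question readers will bring to the results. If the data are scored as Table 1 prints and labelled as the moderator plan prints, a benefit in restrained men would be reported as a benefit in unrestrained men, or the reverse. The article plans policy briefs and foresees a contribution to practice guidelines, so a misnamed subgroup could travel beyond the trial report.

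**Working it through.** The plan gives no computed figure on this point to reproduce. The check is one of direction, and the sample size of 56 per group does not enter it.

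**Inputs.** Six items, each scored 1 (strongly disagree) to 4 (strongly agree), from Table 1. Cut at 2, with the labels as quoted, from the Moderator analysis plan.

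**1. Which score is meant.** The sum of six items runs from 6 × 1 = 6 to 6 × 4 = 24. No man can have a sum below 2, so the cut makes sense only for the item mean, m = sum / 6, which runs from 1.00 to 4.00. The article does not state this; it is inferred.

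**2. Who falls in each group on the printed anchors.**
- m < 2 requires a sum of 6 to 11, so m runs from 6/6 = 1.00 to 11/6 = 1.83. This is the lowest third of the range, since (2 − 1)/(4 − 1) = 1/3. These men reject restraint items, yet the plan labels them as having greater restraint.
- m ≥ 2 requires a sum of 12 to 24, so m runs from 12/6 = 2.00 to 24/6 = 4.00. This group includes every man who strongly agrees with all six items, yet the plan labels it as having lower restraint.

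**3. What would rescue the labels.** Suppose the whole subscale is reversed, x′ = 5 − x for each item, so m′ = 5 − m. Then m′ < 2 is the same as m > 3 on the printed anchors. Those men do endorse restraint, and the labels would be right. No constant shift of the anchors and no change between sum and mean has this effect; only whole-scale reversal does.

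**4. Comparison with the other score cuts in the same sentence.** For nature connection the plan gives "score, weak (<5) vs moderate-to-strong (5" and above), which agrees with the scale in Table 1, where agreement scores high. For baseline distress the lower DASS-21 scores (below 41) are called normal to mild, which agrees with the Primary outcome section, where higher is worse. Emotional control is the only numeric cut whose labels oppose its scale.

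**5. What the labels can and cannot change.** Let M = 1 if m ≥ 2 and 0 otherwise. Replacing M by 1 − M changes the sign of the group-by-moderator coefficient but not its absolute size, its standard error or its p value. The estimate within each set of men is also the same. Only the name attached to each set changes.

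**6. The baseline-only listing.** The Primary analysis plan fits arm, visit and their interaction to the secondary outcomes. With a single measurement before randomisation there is no visit effect and no interaction to estimate, so no programme impact on emotional control can be shown.

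**The case against.** The strongest reply is that Table 1 prints response anchors and one of six items, not a scoring rule. A journal article commonly leaves scoring to the full protocol or analysis plan, which is not shown. If the subscale is scored in reverse, the labels are correct and Table 1 is merely incomplete. The position of the cut gives this some weight: the midpoint of a 1–4 mean is (1 + 4)/2 = 2.5, so a man who answers 2 to every item, still nearer the disagree end, would fall in the greater-restraint group once the labels are swapped. Under reversal the greater-restraint group would be men with a mean above 3 on the printed anchors, which is a coherent group.

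That argument stands against treating the label swap as the certain remedy. It does not remove the contradiction: as printed, the two places cannot both be followed, and nothing in the article tells the analyst which governs.

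It is also fair to say that this is one of five moderators, given no special rank in the plan, and that its subgroup analysis runs only if the interaction reaches the stated threshold. The rationale also rests on physical activity, nature exposure and reduced formality.

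A reader might infer that the moderation test itself would come out wrong, that every moderator result is affected, or that the trial's main conclusion is at risk. The article supports none of these. The test and the estimates do not depend on the labels, the other numeric cuts are labelled in line with their scales, and the primary hypothesis, outcome, sample size and model do not use this variable.

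**Conclusion.** The labels for the emotional-control subgroups contradict the scale direction in Table 1. Followed as written, the plan would name both subgroups backwards for this moderator. The interaction p value and the subgroup estimates would be unchanged; the statement of which men benefit would be inverted.

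This rests on three assumptions: that the score is the 1–4 item mean, that any oppositely worded items are recoded to the direction of the example item, and that the printed labels are carried into the analysis. An unstated whole-scale reversal, or a slip confined to the article, would avoid the misattribution but would still leave the published plan needing correction. The article does not settle which of the two places is at fault, so it would go too far to say that a wrong conclusion is certain.

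The listing of a baseline-only measure as a secondary outcome and programme impact is a real but minor inconsistency. Table 1 shows openly that there is no later measurement, so it is unlikely to mislead the analysis.

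**What to change.** Before the moderator analysis is run:

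1. State how the subscale is scored: the item mean on 1–4, which direction is high, and any reverse-keyed items.
2. Make Table 1 and the Moderator analysis plan agree. If the scoring is as the printed anchors imply, relabel so that scores below 2 are lower restraint and scores of 2 and above are greater restraint. If the subscale is in fact scored in reverse, keep the labels and state the reversal in Table 1.
3. Check whether the registered definition of this moderator carries the same labels, and correct it with a dated note if it does.
4. List emotional control as a baseline moderator, and remove it from the secondary outcomes in Table 1 and from the impacts in the Discussion.

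The cost is wording only, with no new data and no change to sample size, model or test. Timing matters: the Study design section says that post-intervention assessments are complete and 12-month follow-up is under way. A correction dated before the analysis is plainly clerical, whereas the same swap made after results are seen could look driven by the data.

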#### Cost-effectiveness analysis plan

A trial-based cost-utility analysis will be undertaken from the perspective of the health service over a 12-month period. Health utility of patients over the duration of the study will be derived from their SF-12 scores, and quality-adjusted life-years gained will be calculated. Costs of the intervention and health service use will be compared across the two groups and an incremental cost-effectiveness ratio (showing differences in costs and quality-adjusted life years gained) will be calculated. Sensitivity analyses, including probabilistic analyses will be used to assess the robustness of results to uncertainty in estimates of costs and health outcomes.

## Ethics and dissemination

This study has been approved by the University of Newcastle Human Research Ethics Committee (H-2024-0090). The investigators and staff named on the ethics approval will analyse the data and write the trial manuscript. We intend to publish results in an open access peer-reviewed journal as soon as practicable after study completion. Findings will be disseminated through community-facing presentations and presentations at national and international academic conferences. In addition, policy briefs will be prepared and shared with relevant stakeholders to support translation of findings into practice.

## Discussion

Given over 100 million men worldwide are affected by depression,^49^ and at least one in eight Australian men experience it annually,^5^ yet less than 40% attend therapy with nearly half discontinuing prematurely,^16^ there is an urgent need to evaluate novel approaches to engage and assist men experiencing poor mental health. Walk-and-talk therapy, which integrates physical activity with psychological support in outdoor environments, has emerged as a promising approach to address these challenges.^50
51^ This protocol outlines our study that aims to compare the effectiveness of walk-and-talk therapy to conventional indoor therapy on overall psychological distress in men with depressive symptoms. Despite the clear need for targeted therapy approaches for men, this study will also be one of the only clinical trials specifically targeting men with depression in the past decade.^24^

Strengths of this study protocol include a randomised design with an active intervention control group (conventional indoor therapy), a preregistered, detailed statistical analysis plan that will follow the intention-to-treat principle and the inclusion of a 12-month follow-up to measure the longer-term treatment outcomes. In addition to measuring overall psychological distress (depression, anxiety and stress), a comprehensive range of secondary outcomes will also be assessed to capture other psychological (male-type depression symptoms, mental well-being, suicidal ideation, quality of life), behavioural (physical activity, sleep, nature contact), social (nature connection, emotional control, engagement in valued activities, mental restoration) and economic (costs) impacts of the programme. By successfully completing this trial, insights into the efficacy of an innovative psychotherapy approach for men will be generated through various analytical methods (eg, mediation and moderation analyses). Lastly, recruitment efforts will focus on men residing in areas identified as socio-economically disadvantaged to ensure a diverse sample. Limitations of the current study include reliance on psychologist self-report to assess adherence to the therapy modality, as sessions are not independently coded. This approach was necessary due to the practical challenges of recording sessions in outdoor settings; however, it may introduce bias into the fidelity assessment. Furthermore, data relating to therapist favourability to a particular therapy setting were not collected, which may represent an additional source of bias; future trials building on this work would benefit from collecting therapist allegiance data to enable assessment of its potential influence in sensitivity analyses. The power calculation did not account for therapist-level clustering; the extent to which this affects statistical power will depend on the magnitude of the therapist-level intraclass correlation coefficient, which will be reported alongside the trial outcomes. In addition, participants self-select into a trial conducted at a university campus, which may limit generalisability to other clinical populations and health service settings. Individuals who are willing to participate in such trials may be more motivated or more receptive to novel therapeutic approaches than the general population. As such, further research will be needed to evaluate this intervention when implemented within routine care contexts.

This study will provide new evidence on the effectiveness, safety and cost-utility of two alternative therapeutic approaches, informing whether walk-and-talk therapy should be integrated into routine health practice. Should walk-and-talk therapy demonstrate comparable or superior outcomes to conventional indoor therapy, findings may support its adoption as an alternative therapeutic option within existing psychological services and/or inform the development of practice guidelines. In particular, offering therapy in outdoor settings may improve engagement among men who are less likely to access or remain in traditional clinic-based psychotherapy. Although our study focuses on efficacy rather than implementation, we have collaborated closely with end-users, including registered psychologists, men with lived experience (EW) and health service managers. This collaboration ensures that our study addresses important considerations for men with depression and tests an intervention with realistic potential for health service implementation. Lastly, regarding cost-utility, economic evaluations conducted alongside clinical trials are increasingly recommended to inform health policy and resource allocation in mental health services.^52^ While there is currently limited evidence regarding nature-based therapeutic interventions’ economic value relative to traditional psychotherapy, there is some evidence for its potential cost-effectiveness for people with mild to moderate common mental health problems but significant further research is required.^53^
